## Supplement 1. Study Protocol

the burden brought by COVID-19 pandemic. The study findings highlighted the potentials of delivering psychosocial interventions through telehealth approach (36).

In their Monitor and Acceptance Theory (MAT), Lindsay and Creswell (2017) posit that MF increases cognitive functioning by enhancing individuals' awareness of their experiences and reduces negative affective reactivity by increasing acceptance (42). Based on MAT, Lindsay et al. developed a 2-week smartphone-based MF RCT with 14 daily sessions and tested it in an adult sample in the US. This intervention effectively reduced loneliness by 22% and increased social interaction by 2 times per day among the participants (20). However, the participants in this RCT were not older adults. There was also no follow-up after the completion of the intervention, which makes it difficult to draw conclusions about its long-term effectiveness. Therefore, we aim to evaluate the effectiveness of a telephone-delivered MF (Tele-MF) intervention in reducing loneliness among older adults in Hong Kong by adopting the intervention materials from Lindsay et al. (20). We aim to examine the short- and long-term effectiveness of the intervention with follow-up assessments at 4 weeks, 3 months, and 6 months post-intervention.

### **Delivering an Intervention by Telephone and by Trained Lay Volunteers**

There are significant challenges to in-person delivery of interventions to reduce loneliness in older adults. Many older adults face transportation problems. Deploying interventionists for in-home sessions with older adults is very costly, and therefore not sustainable and scalable. In light of these challenges of in-person delivery, recent intervention programs have used technology as a way to reduce loneliness and social isolation in older adults (see (43) for a scoping review). In addition to the aforementioned examples by Choi et al (2020) and Lindsay et al. (2019), Tsai et al. (2020) also developed a smartphone-based videoconferencing program allowing nursing home residents to contact their families through video calls in Taiwan (44). The results of this 6-month intervention study revealed that the level of loneliness of residents in the intervention group significantly reduced compared to that of residents in the control group. Older veterans who received a telephone-delivered social activity intervention, as well as older adults who received telephone-delivered BA for depression during the COVID-19 pandemic rated telephone delivery as highly acceptable (33,45). Given the high contagiousness of the SARS-CoV-2 virus, use of telephone or videoconferencing has been found to be an especially useful and inexpensive approach to reducing the levels of loneliness and social isolation of older adults during the pandemic when social/physical distancing measures were in place (43).

Along with telephone delivery, nonprofessional delivery of mental health interventions is an important area of research given the global shortages of professional mental health workers. Unlike other psychotherapeutic approaches that rely heavily on mental health clinicians, studies have demonstrated that BA can be delivered by trained volunteers or lay counselors with a bachelor's degree (17,46–48). Therefore, we proposed to compare the effectiveness of telephone-delivered BA and MF interventions (hence Tele-BA and Tele-MF) by trained volunteers (see study protocol for volunteers part for the trial Warner et al., under

## Supplement 1. Study Protocol

review(49) to that of telephone-delivered befriending (Tele-BF, i.e., providing emotional support) (50,51) as an active control in reducing loneliness in older adults.

### Study Objectives and Hypothesis

The COVID-19 pandemic has undoubtedly imposed a wide range of restrictions on older adults' participation in social activities, increasing their level of loneliness. Low-income older adults who live alone and have limited access to the Internet are at higher risk of loneliness (52,53). Our primary aim is to evaluate whether a Tele-Behavioral Activation (Tele-BA) and a Tele-Mindfulness (Tele-MF) intervention are more effective than the active control consisting of Tele-Befriending (Tele-BF) in reducing loneliness (i.e., one of the primary outcomes, see below for details on all measures) among community-dwelling older Chinese adults in Hong Kong who live alone and in poverty and have limited access to the Internet. Tele-BA focuses on increasing and reinforcing a target individual's engagement in meaningful life activities (31), Tele-MF focuses on increasing awareness of the present moment with acceptance (20), whereas Tele-BF refers to a volunteer's provision of emotional support for the target individual who reports loneliness (50). We hypothesize that Tele-BA and Tele-MF interventions are effective in reducing perceived loneliness, measured at the 4-week, 3-month, 6-month, and 12-month follow-up assessments, compared to Tele-BF group.

### Method/design

#### Research Integrity

Ethical approval for this proposed project was obtained from the Human Research Ethics Committee of the Education University of Hong Kong (reference number: 2019-2020-0442). The study was prospectively registered in the Clinical Trials Registry of the University of Hong Kong Clinical Trials Centre (HKU-CTC) (registration number: HKUCTR-2929) and retrospectively registered at the Chinese Clinical Trial Registry in the WHO Registry Network, number ChiCTR2300072909). The contents of the two registrations were identical.

#### Participant Recruitment and Eligibility

This study protocol targets community-dwelling Chinese older adults. The inclusion criteria are as follows: (a) age 65 and older; (b) living alone; (c) living in poverty (i.e., monthly income < HKD 4,500 or USD 577); (d) able to communicate in Cantonese by telephone; (e) mild or no cognitive impairment; (f) no psychiatric disorder; (g) no Internet at home; (h) not engaged in regular mindfulness or a related mind-body practice; and (i) feeling lonely (score of 6 or higher on the three-item UCLA Loneliness Scale, Lin et al., 2020). Participants have been recruited through community centers for older adults, older-adult academies, and from public housing estates. The study's purpose, time commitment for participation, voluntariness, right to quit without negative consequences, and inclusion criteria have been clearly presented before a participant gives verbal consent to participate. Older adults who meet the above criteria have then been asked to sign a written informed consent form. The current stage of the study is that interventions and follow-up assessments are under way.

## Supplement 1. Study Protocol

### Sample Size

A required sample size for the RCT on loneliness was estimated for one of the primary outcomes, that is, loneliness assessed by UCLA Loneliness Scale (54). A previous intervention study on reducing loneliness in older adults yielded an effect size of 0.5 (31). To be more conservative, we estimate the sample size based on a smaller effect size, i.e., 0.25. To detect an effect size of 0.25 at an alpha error rate of 0.05 and a power of 90%, the estimated sample size is 289 participants in each group. With an anticipated drop-out rate of 10% over a period of 6 months, the necessary sample size is 322 participants per group at baseline ( $N=966$  in total).

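### The stated sample-size inputs (effect size 0.25, alpha 0.05, 90% power) do not yield 289 per group; under a conventional two-sided comparison 289 is the number for 85% power

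*Protocol*

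**What the plan says.** The Sample Size section of the protocol sizes the trial on loneliness measured by the UCLA scale. It starts from an effect size of 0.5 in an earlier trial and halves it: "we estimate the sample size based on a smaller effect size, i.e., 0.25". It then gives the calculation as "an effect size of 0.25 at an alpha error rate of 0.05 and a power of 90%, the estimated sample size is 289 participants" per arm. The drop-out step follows: "With an anticipated drop-out rate of 10% over a period of 6 months", the baseline requirement becomes 322 per group, or 966 in total.

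The section does not say whether the test is one- or two-sided, which test is meant, which effect-size metric 0.25 is, or whether a correlation between repeated measurements was used. Study Objectives and Hypothesis compares each of the two interventions with Tele-BF, with loneliness "measured at the 4-week, 3-month, 6-month, and 12-month follow-up assessments".

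**The concern.** A sample-size statement should reproduce from its own inputs. This one does not under the reading that most readers will apply, and the number printed coincides with the answer for a lower power. If 85% is the true figure for the calculation that was done, the type II error at an effect of 0.25 is about 15% rather than 10%. This matters most if the trial finds no difference. The comparator is an active befriending control, so that outcome is a real possibility, and readers would credit the trial with more power against a difference of 0.25 than this calculation supports.

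**Working it through.** **Inputs (Protocol, Sample Size):** effect size 0.25, alpha 0.05, power 90%, 289 per group, 10% drop-out. Equal allocation is implied by the equal group sizes.

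**Assumptions (not in the protocol):** 0.25 is a standardized mean difference d; the test is two-sided; each intervention is compared with Tele-BF at one time point without covariates.

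**1. The drop-out step reproduces.** 289 / (1 − 0.10) = 321.1, rounded up to 322; 3 × 322 = 966. Any fault lies in the 289 or in the power attached to it.

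**2. Number needed for 90% power.** n per group = 2 × (z for 1 − alpha/2 + z for power)² / d²
- 90%: 2 × (1.960 + 1.282)² / 0.0625 = 32 × 10.51 = 336.2, so 337. The noncentral t gives 337.2, so 338.
- 85%: 2 × (1.960 + 1.036)² / 0.0625 = 32 × 8.98 = 287.3, so 288. The noncentral t gives 288.3, so **289**, the printed figure.

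**3. Power at 289.** d × √(n/2) = 0.25 × √144.5 = 3.005, and 3.005 − 1.960 = 1.045. The normal approximation gives 85.2%; the noncentral t gives 85.1%.

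**4. Effect for which 289 gives 90%.** (1.960 + 1.282) × √(2/289) = 3.242 × 0.0832 = 0.27.

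**5. Other readings.**

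| Reading | n per group for 90% | Power at 289 per group |
|---|---|---|
| Two-sided 0.05, two groups | 338 | 85.1% |
| One-sided 0.05, two groups | 275 | 91.3% |
| Two interventions pooled 2:1 against control, two-sided 0.05 | 253 (control group) | 93.4% |
| Three-group ANOVA, f = 0.25 | 69 | above 99.9% |
| Three-group ANOVA, f = 0.125 | 271 | 91.9% |
| Three-group ANOVA, both interventions 0.25 better than control (f = 0.118) | 305 | 88.3% |
| Three-group ANOVA, means evenly spread over 0.25 (f = 0.102) | 406 | 77.1% |

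None of these returns 289 at 90% power.

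**6. Baseline adjustment.** Adjusting for baseline multiplies n by (1 − r²). To bring 337 down to 289, r² = 1 − 289/337 = 0.142, so r is about 0.38. That value is not implausible, but the section states no correlation and no adjustment.

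**7. Time horizon.** The 10% allowance covers 6 months. The hypothesis, the assessment schedule in Study Design and the Group × Time model in the planned analysis all include 12 months. No drop-out figure is given for the period after 6 months.

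**The case against.** The strongest reply is that the section never says two-sided. The primary aim is directional, and at one-sided 0.05 the power at 289 is 91.3%, so the stated 90% would be met. The planned analysis is also a repeated-measures mixed model that includes baseline, so its power depends on a correlation the protocol does not give and could exceed 85%. Both points stand, and they limit the claim. A reader might infer that the trial's true power is 85% whatever the analysis; the protocol does not establish that. What it does establish is that the printed inputs do not give the printed output. The one-sided reading does not rescue the calculation, because it would have led to 275.

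Two further inferences go too far. One is that the 6-month drop-out allowance is an arithmetic error. It is not: the inflation is correct, and nothing in the protocol claims 90% power at 12 months. If 12-month attrition were 15%, 20% or 25% (assumed values, not in the protocol), a completers-only two-sided comparison from 322 per group would have about 83%, 81% or 78% power. The mixed model keeps participants with partial data, so these figures illustrate the direction but do not describe the planned analysis. The other inference is that power should be quoted at an alpha divided between the two comparisons; the protocol contains no such division.

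Finally, recruitment ended on 30 April 2023, and no estimate, test or participant procedure depends on this paragraph. That bears on severity, not on whether the statement is right.

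**Conclusion.** Wrong as written, of moderate severity. An effect size of 0.25, alpha 0.05 and 90% power do not give 289 per group. If the calculation was a two-sided, unadjusted two-group comparison of a standardized mean difference, the requirement was 338, and 289 gives 85.1% power at 0.25 or 90% at about 0.27. The exact match with the 85% requirement suggests that the number was computed for 85% and labelled 90%, but the protocol cannot confirm this. A one-sided test would meet the stated power without explaining the figure. A baseline correlation of about 0.38 would explain it but is not stated. The 12-month point amounts to a note on what period the stated power refers to.

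**What to change.** Do not enrol more participants. Replace the sentence in Sample Size with one of the following:

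- 289 evaluable participants per group give 85% power for each comparison with Tele-BF at d = 0.25 (two-sided 0.05, unadjusted two-group comparison), or 90% power at d = 0.27.
- If a one-sided test or a baseline correlation was used, name it, give its value and state the power that it gives at 289 per group.

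Add one sentence saying that this power refers to 6 months, with 10% drop-out, and that the 12-month comparison has no attrition allowance beyond that.

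The cost is a few sentences. Under the first option the stated power becomes less favourable. Group sizes, the drop-out step and the analysis do not change.

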### Study Design

Participants are interviewed by trained assessors using structured questionnaires at five time points: at baseline (pre-intervention) and at 4 weeks, 3 months, 6 months, and 12 months post-intervention. The baseline, 6-month, and 12-month follow-up assessments are conducted face-to-face, while the other two assessments are conducted over telephone. Because of the specific questions related to each intervention modality, volunteer callers cannot be blinded to the intervention modality, but they will be blinded to the study hypotheses. The intervention duration for the Tele-BA, Tele-MF, and Tele-BF groups is 4 weeks, with two sessions per week of approximately 30 minutes each (i.e., eight sessions in total). All intervention sessions are conducted by trained volunteers via telephone.

### Randomization

After completing baseline assessment, participants are randomly assigned to either Tele-BA, Tele-MF, or Tele-BF using an online random number generated by a research assistant. Participants are then informed of their assigned intervention, and Tele-BA participants receive copies of BA worksheets. Due to the nature of the intervention, participants cannot be blinded as the types of activities in each intervention group are distinct.

### Volunteer Training and Training Materials

Tele-BA intervention was adapted from the Telehealth Behavioral Activation Treatment Manual for Homebound Older Adults (55). The Tele-MF intervention was adapted from the smartphone-delivered mindfulness intervention developed by Lindsay et al. (2019) to reduce loneliness in stressed adults (20). The Tele-BF active control condition was adapted from the BEFRIENDAS: Befrienders Information Guide by the National Ageing Research Institute (2020) (51). Each intervention includes eight sessions, with two sessions per week of approximately 30 minutes each, summing up to a four-week intervention period in total.

One experienced social worker and one research assistant are hired to deliver training sessions for Tele-BA, Tele-MF, and Tele-BF volunteers separately, making sure that the volunteers adhere to the respective intervention manual developed by the research team. Each volunteer is required to attend 6 weekly training sessions (2 hours per week) before they can independently conduct the intervention with older adults. A small group format, with four to six volunteers, is used to include role plays and practice in each session. The research

## Supplement 1. Study Protocol

team worked closely with the two trainers to prepare PowerPoint presentations to ensure comparability of the training content across small groups within the same intervention program.

### **Intervention Procedures and Delivery**

#### ***Experimental Condition 1: Tele-BA***

BA intervention covers a set of strategies to improve older adults' mood by (a) learning skills to help change daily behaviors, (b) cultivating new healthy behaviors, and (c) identifying and changing patterns of avoidance, withdrawal, and inactivity.

The first session provides an introduction to BA and describes the worksheet to record participants' daily activities. The second session focuses on behavioral monitoring and identification of important and meaningful life domains and goals. In the third session, participants are guided to select and plan the most rewarding activities to accomplish their chosen goals, and it is explained how to seek support for difficult activities. In the fourth session, participants are supported to identify and overcome barriers to implementing their selected activities. In the fifth session, participants are encouraged to find ways to maintain the benefits after the intervention program. In the sixth session, participants' behavioral monitoring and activity planning for the coming week is reinforced. In the seventh session, problem-solving and maintaining the benefits obtained after the end of the program are discussed. In the last session, participants' learning goals are reviewed, their successes are celebrated, and continued BA practice in daily life is discussed.

BA volunteers play an active role in the intervention to change participants' negative cognitive processes. In particular, they guide older adults to develop skills to manage their isolation and loneliness, cultivate confidence in their ability to do more than they think they can, and encourage them to take part in meaningful and pleasant activities.

#### ***Experimental Condition 2: Tele-MF***

Tele-MF intervention is based on the smartphone-delivered mindfulness intervention developed by Lindsay et al. (2019) to reduce loneliness in stressed adults (20). The intervention aims to reduce loneliness and increase social interaction by cultivating two mindfulness skills: mindfulness orientation and present monitoring. To standardize Tele-MF intervention condition with the other two conditions (Tele-BA and Tele-BF), we modified the original approach of Lindsay et al. (2019) from 14 sessions of 20 minutes each (delivered over a period of 8 weeks) to 8 sessions of 30 minutes each (delivered over a period of 4 weeks) and from a smartphone app to a telephone-based intervention. Thus, eight telephone sessions are delivered to each participant.

In the first session, the concept of mindfulness is introduced. In the second session, body focus techniques with closed and open eyes are practiced. In the third session, participants learn how to focus on their body when listening to others talk. In the fourth session, participants learn how to focus on their body and mind using the verbal and mental labels of "feel" (i.e. the entire range of experiences in one's body, including affective states, body sensations, energy flow sensations, etc). In the fifth session, participants learn to feel the experiences

## Supplement 1. Study Protocol

of their body while maintaining equanimity by keeping their body relaxed. In the sixth session, participants learn to distinguish different types of sensations, levels of intensity, and spatial patterns and to detect subtle body events. In the seventh session, participants practice to deepen equanimity by maintaining a positive attitude toward stress. In the final eighth session, the content of the training is summarized in an appreciative way and ways to continue MF practice are discussed.

### **Active Control Condition: Tele-BF**

BF refers to regular contact between a volunteer who acts as or becomes friends with older adults. BF consists of a series of conversations between the participant and the volunteer, which are often related to everyday topics and events, such as hobbies, TV programs, cooking, books, or movies (56). Because BF aims at increasing communication and providing emotional support, but not other psychological processes, it has been widely used as the active control group in interventions on reducing loneliness (51). In this proposed study, a total of eight BF sessions for four weeks, each session lasting approximately 30 minutes.

The first session includes an introduction to BF and a self-introduction of the participant and the volunteer. For the second to eighth sessions the following specific conversation topics are suggested: second session, favorite TV programs; third session, diets, cooking, and favorite foods; fourth session, current news events or a memorable recent event; fifth session, weather and favorite season; sixth session, favorite soup; seventh session, favorite holiday and celebration activities; and eighth session, favorite places and conclusion.

### **Materials and Measures**

Structured questionnaires are used to assess participants at baseline and 4 weeks, 3 months, 6 months, and 12 months post-intervention. Table 1 shows an overview of timeline and measures in this study.

### **Primary Outcomes**

Table 1 shows an overview of timeline and measures. Loneliness and perceived social support are the primary outcomes of the intervention.

**Loneliness.** Loneliness is measured by the De Jong Gierveld Loneliness Scale (56) and the 20-item Revised UCLA Loneliness Scale (58). The validated Chinese version of the De Jong Gierveld Loneliness Scale (Leung et al., 2008), consisting of six items, is adopted to measure retrospective loneliness. Participants are asked to indicate their level of agreement with the six statements on a 3-point scale (1 = yes, 2 = more or less, 3 = no). Sample items include “I experience a general sense of emptiness,” “Often, I feel rejected,” and “I miss having people around.” Means and standard deviations will be used in data analysis. The statements will be reversely scored with higher values representing higher loneliness.

The Revised UCLA Loneliness Scale (58) comprises 20 items to assess loneliness and has been validated among Chinese adolescents (59). This version improved from the original UCLA Loneliness Scale (60) by addressing concerns on the direction of the items, discriminant validity, social desirability (58). Each

## Supplement 1. Study Protocol

item in the Revised UCLA Scale is a question starting with “How often do you feel?” Participants are asked to indicate how often they think each question describes their experiences on a 4-point scale (1 = never to 4 = always). Sample items include “How often do you feel alone?”; “How often do you feel that there is no one you can turn to?”; and “How often do you feel that you are no longer close to anyone?”. Items are averaged with higher score indicating higher perceptions of loneliness.

**Perceived Social Support.** Perceived social support is assessed using the Chinese version of the 12-item Multidimensional Scale of Perceived Social Support (MSPSS) (61,62). The MSPSS asks participants to indicate their level of agreement with 12 items on a 7-point scale (1 = strongly disagree to 7 = strongly agree). Sample items include “I get the help and support I need from my friends,” “I get the emotional help and support I need from my family,” and “My family is willing to help me make decisions.” Answers on all 12 items will be averaged to derive a total score of perceived social support, with higher values representing higher perceived social support.

